## Abstract

**Background:**

Motion sensitivity after vestibular disorders is associated with symptoms of nausea, dizziness, and imbalance in busy environments. Dizziness and imbalance are reported in places such as supermarkets and shopping malls which have unstable visual backgrounds; however, the mechanism of motion sensitivity is poorly understood.

**Objective:**

The main aim of this exploratory observational study is to investigate visual fixations and postural sway in response to increasingly complex visual environments in healthy adults and adults with motion sensitivity.

**Methods:**

A total of 20 healthy adults and 20 adults with motion sensitivity will be recruited for this study. Visual fixations, postural sway, and body kinematics will be measured with a mobile eye tracker device, force plate, and 3D motion capture system, respectively. Participants will be exposed to experimental tasks requiring visual fixation on letters, projected on a range of backgrounds on a large screen during quiet stance. Descriptive statistics (mean and standard deviation) will be calculated for each of the variables. One-way independent-measures analyses of variance will be performed to investigate the differences between groups for all variables.

**Results:**

Data collection was started in May 2019 and was completed by February 2020. It was approved by Health and Disability Ethics Committees, Ministry of Health, New Zealand on November 2, 2018 (Ethics ref: 18/CEN/193). We are currently processing the data and will begin data analysis in July 2020. We expect the results to be available for publication by the end of 2020. The trial was funded by the Neurology Special Interest Group, Physiotherapy New Zealand, and the Eisdell Moore Centre in November 2018.

**Conclusions:**

This study will provide a detailed investigation of visual fixations in response to increasingly complex visual environments. Investigating characteristics of visual fixations in healthy adults and those with motion sensitivity will provide insight into this disabling condition and may inform the development of new intervention strategies which explicitly cater to the needs of this population.

**Trial Registration:**

Australian New Zealand Clinical Trials Registry, ACTRN12619000254190; https://tinyurl.com/yxbn7nks

**International Registered Report Identifier (IRRID):**

PRR1-10.2196/16805

## Introduction

Motion sensitivity is characterized by nausea, dizziness, and imbalance in response to motion of the visual environment [1]. It can develop as a sequela of a vestibular disorder and is one of the diagnostic criteria for persistent postural perceptual dizziness [1-3]. The symptoms are due to a misinterpretation of, or overreliance on, visual cues for orientation in space [1,3-6]. Dizziness and imbalance are triggered in busy surroundings with visual motion or complex repetitive patterns. Consequently, people with motion sensitivity tend to avoid crowded or busy environments such as supermarkets or driving on motorways [7]. This frequently leads to an interruption of daily activities, sick leave from work, and in extreme cases a reluctance to leaving the house [8,9]. Motion sensitivity may affect people following an acute vestibular insult or people with chronic recurrent dizziness [10].

Information from the visual system has a role in differentiating self-motion from external motion [11]. This differentiation is dependent on perceiving whether motion on the retina is due to an object moving relative to the person or the person moving relative to the object [12,13]. This distinction between self-motion and external motion is achieved by a mechanism that compares the retinal signal and the reference signal. The reference signal comprises information from vision, vestibular afferents, proprioceptive feedback from the extraocular muscles, somatosensory kinaesthetic proprioception, and cognition [14] (Figure 1).

**Figure 1 figure1:**
[figure not shown]
The sources of information to allow differentiation of self-motion and object motion components. The various sources are shown as giving information with respect to different reference frames.

A crucial aspect of the stabilization of posture is dependent on the visual input received from the environment. An essential component of visual input is optic flow [15,16]. Optic flow helps perception of spatiotemporal information from the environment which is then used to move around and maintain orientation in space [12,17]. Optic flow generates retinal slip, defined as motion of the visual image of the environment on the surface of the retina [18]. This information is used to adjust the amount of postural sway. The main aim of visually induced postural movements is to reduce the overall amplitude of the optic flow field by minimizing retinal slip [19-21].

Because optic flow plays a vital role in postural correction, perceiving inaccurate information can be destabilizing. Optic flow that is a part of the background motion behind a target is not normally used as a visual input for postural control as it can stimulate an optokinetic response (which evokes a combination of a slow-phase and fast-phase eye movements where the eyes momentarily follow the moving object and then rapidly reset back to the initial position) [22]. This response can induce a standing subject to move in response to the direction of the motion and can be destabilizing [22]. In normal circumstances, this optokinetic response to background motion is suppressed by visually fixating on a target [23].

Visual fixations contribute to 80% of the total visual experience [24], and help to reduce optic flow, minimize retinal slip, and suppress the optokinetic response [23]. When fixating on a stationary target, there is almost no retinal slip, and the vestibulo-ocular reflex keeps the gaze on target during head movements [21]. By contrast, maintaining fixation on a moving object requires suppression of the vestibulo-ocular reflex for the eyes and the head to move in the same direction [21,25,26].

Fixations contribute to a person’s sense of spatial orientation. Fixations suppress visual field motion perception by maximizing the peripheral vision and rendering a stable image to enhance the visual signals of self-motion [27]. Sensations of small body movements then facilitate the execution of compensatory postural reactions [28].

Fixational instability may predispose a person to develop motion sensitivity [29-31]. Studies have shown that people with motion sensitivity after vestibular disorders exhibit fixational instability and have increased perceptual and postural responses to complex visual surroundings [31-34]. Several studies have investigated the relationship between fixational instability and the strength of illusionary motion [29-31]. Fixational instability can be detected by frequency of refixations and saccades [32,34]. Studies have reported that a person with fixational instability would have a high frequency of saccades and refixations while attempting fixation [32,34].

Any difficulty in differentiating self-motion from external motion will require adjustments to determine the correct orientation in space. A peripheral or central vestibular disorder disrupts the normal visual–vestibular interaction [35], which can alter the perception of motion. It can lead to illusionary motion perception, thereby degrading postural stability. Adults with motion sensitivity report worsening of symptoms and reduced postural control in visually stimulating environments which may be explained by fixation instability. However, to date, visual fixations have not been well investigated in people with motion sensitivity. Previous studies have used video oculography or electrooculogram and optokinetic stimulation rotating around the naso-occipital center to study eye movements in adults with motion sensitivity [32-34]. This study aims to investigate the characteristics of fixations in people with motion sensitivity and how they differ from those of healthy adults by using a mobile eye tracker device in a more naturalistic yet controlled laboratory setting.

This research will investigate visual fixations, postural sway, and kinematics of adults with motion sensitivity, compared with healthy adults, in complex visual environments. Center of pressure (COP) measurement will be used to evaluate postural sway. COP parameters have been used widely to describe stability and quantify alterations in postural control [36,37]. The exploratory nature of this study will also allow the investigation of mean saccadic velocity and saccadic peak amplitude between groups. Several studies have identified anomalies in mean saccadic velocities in a range of health conditions [38,39].

This study is the first step toward recognizing the components that may be essential in a rehabilitation programme addressing the challenging clinical issue of motion sensitivity and may guide the development of rehabilitation programs for adults with motion sensitivity.

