### Hypothesis

Complex visual environments in people with motion sensitivity compared with healthy adults will be associated with (1) increased number of visual refixations, (2) increased displacement of COP, and (3) differences in the body COM displacement and differences in the head COM displacement.

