#### Visual Fixations

Fixation characteristics for each group will be computed using the SMI ETG software and will measure the total number of refixations, the maximum fixation duration, and the number of saccades. The software determines a fixation as a window with a minimum duration of 80 ms and a maximum dispersion of 100 pixels. Refixations are calculated if the eye crosses the maximum dispersion threshold of 100 pixels. The fixation duration will be calculated as the total time spent in fixating during a trial. The maximum fixation duration will be calculated as the longest fixation within each trial. A saccade event is computed as any event that does not meet the fixation criteria between the new and the previous fixation.

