#### Analysis

Descriptive statistics (mean and standard deviation) will be calculated for each of the variables. Data normality will be examined using the Kolmogorov–Smirnov statistic. One-way independent-measures analyses of variance will be performed to investigate the differences between groups for all variables. Post-hoc analysis with Šidák adjustment will be used for multiple comparisons [48]. Finally, a receiver operating characteristic curve analysis will be applied to determine threshold values in gaze, COP, and COM parameters, allowing identification of the impairment induced by motion sensitivity. The optimal cutoff point will be determined using the Youden Index. Areas under the curve, specificity, and sensitivity will also be calculated. Values of areas under the curve will be categorized as follows: excellent (≥0.90), good (0.80-0.90), fair (0.70-0.79), and poor (<0.70).

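### Exploratory mean saccadic velocity: the unadjusted group mean pools letter-to-letter shifts with refixations, so the groups may differ through saccade mix alone, most likely as apparent slowing in cases

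*Protocol article*

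**What the plan says.** Saccadic velocity appears once, in the Introduction: "The exploratory nature of this study will also allow the investigation of mean saccadic velocity and saccadic peak amplitude between groups". The reason given is that "Several studies have identified anomalies in mean saccadic velocities in a range of health conditions". Neither velocity nor amplitude appears in the Hypothesis section or among the eye measures under Outcome Measures, Visual Fixations. Those measures are the number of refixations, maximum fixation duration and number of saccades.

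Four other statements determine how velocity would be handled:

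- **Test** (Statistical Analysis, Analysis): "One-way independent-measures analyses of variance will be performed to investigate the differences between groups for all variables". No covariate or amplitude band is named. The same section then plans ROC thresholds for gaze parameters, without saying which.
- **Saccade definition** (Visual Fixations): "A saccade event is computed as any event that does not meet the fixation criteria between the new and the previous fixation". A shift to a new letter and a refixation on the current one are the same kind of event.
- **Refixation definition** (same section): "Refixations are calculated if the eye crosses the maximum dispersion threshold of 100 pixels".
- **Expected difference**: the first hypothesis predicts an "increased number of visual refixations" in cases. The Introduction places these movements during attempted fixation: "a person with fixational instability would have a high frequency of saccades and refixations while attempting fixation".

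**The concern.** A larger saccade normally reaches a higher mean velocity, because its duration grows less than in proportion to its size. A participant's mean velocity over a task therefore reflects two things: how fast the eye moves for a given amplitude, and what mixture of amplitudes was made.

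In the single-letter tasks the stimulus program fixes the number of letter-to-letter shifts, and it is the same in both groups. Refixations come on top. If cases make more of them, and they are shorter than the letter shifts, the case mean is weighted towards slower movements and falls with no change in eye dynamics. This would happen even with perfect detection of saccade start and end.

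At stake is interpretation. A velocity difference could be taken for a second oculomotor abnormality, or given a diagnostic threshold, when it only restates the refixation count. Looking at peak amplitude alongside velocity does not remove this, because velocity is still not compared at equal amplitude.

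**Working it through.** The document gives no velocity figure, effect size, alpha or standard deviation, so there is no stated result to reproduce.

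**Inputs from the document**

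- Letter shifts (Experimental Tasks): 70 s per task / 7 s per letter = 10 letters, so 9 shifts per single-letter task (tasks 1, 2, 5 and 6).
- Screen (Experimental Setup): 135 in., 16:9, at 3.5 m. Width 135 × 16/√337 = 117.7 in. = 2.99 m, so 2·atan(2.99/2/3.5) = 46 degrees. Height 1.68 m, so 27 degrees.
- Refixation threshold: 100 pixels. If these are scene-camera pixels over the 60-degree horizontal field, this is 100 × 60/1280 = 4.7 degrees or 100 × 60/960 = 6.3 degrees.

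**Assumptions**

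- Saccade duration is 21 ms + 2.2 ms per degree in both groups, so mean velocity is v(A) = A/(0.021 + 0.0022·A).
- Letter shifts are 15 degrees. Refixations are 5 or 7 degrees, near the threshold. Counts are as tabulated.

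**Mixture calculation**

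v(5) = 156, v(7) = 192 and v(15) = 278 degrees/s. With n refixations of size a, the pooled mean is [9·v(15) + n·v(a)]/(9 + n), where 9·v(15) = 2,500.

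Example, a = 5: for n = 20, (2,500 + 3,125)/29 = 194; for n = 40, (2,500 + 6,250)/49 = 179. The change is −7.9%.

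| Refixations, controls v cases | a = 5 degrees | a = 7 degrees |
|---|---|---|
| 10 v 30 | 214 to 184 (−13.8%) | 233 to 212 (−8.9%) |
| 20 v 40 | 194 to 179 (−7.9%) | 219 to 208 (−4.9%) |
| 20 v 60 | 194 to 172 (−11.3%) | 219 to 203 (−7.0%) |
| 10 v 13 | 214 to 206 (−3.7%) | 233 to 227 (−2.4%) |

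The first three rows, with at least a doubling, give a fall of 4.9% to 13.8%. The last row shows a modest excess.

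**Sensitivity to shift and refixation size**

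Here letter positions are instead drawn uniformly over 80% of screen width and height. Shifts then average 16 degrees (5th to 95th percentile 4 to 31), with mean velocity 264 degrees/s. The comparisons are 5 v 7, 5 v 10, 10 v 20 and 20 v 30 refixations.

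| Refixation size (degrees) | Refixation velocity (degrees/s) | Change in pooled mean |
|---|---|---|
| 4.7–6.3 | 166 | −3.4% to −7.5% |
| 5–10 | 198 | −2.2% to −4.7% |
| 15–20 | 294 | +0.8% to +1.9% |
| 20–30 | 328 | +1.7% to +3.8% |

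The sign reverses once refixations are faster on average than the letter shifts.

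**Simulated one-way ANOVA**

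Settings: 20 v 20 participants, assumed alpha 0.05, identical dynamics, 1,500 runs, assumed between-person coefficient of variation (CV) of velocity 10% or 20%. Entries are the proportion of runs declaring a group difference in the unadjusted mean.

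| Refixation size; counts | CV 10% | CV 20% |
|---|---|---|
| 4.7–6.3 degrees; 10 v 10 | 5% | 4% |
| 4.7–6.3 degrees; 10 v 13 | 12% | 7% |
| 4.7–6.3 degrees; 5 v 10 | 44% | 20% |
| 4.7–6.3 degrees; 10 v 20 | 56% | 22% |
| 15–20 degrees; 10 v 20 | 9% | 6% |

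Dividing each person's mean by the value expected from their own saccade sizes brought the rate to 4.6% to 5.8% in every scenario. That is an idealised adjustment, because the simulation knows the true amplitude relation.

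**The case against.** The strongest reply is that the protocol barely commits to this analysis. Velocity is one exploratory remark in the Introduction and is absent from the aims, hypotheses and listed outcomes. The ANOVA reaches it only through the words about all variables, and the ROC analysis only through the general term for gaze parameters. A fuller plan could condition on amplitude. This stands as a reason for low priority. It does not remove the point: the one comparison the article names has group as its only factor, and the saccade definition pools all sizes.

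Second, a reader might infer that velocity will certainly look slowed, and by a large amount. With 3-degree refixations and counts of 10 v 30 the same formula gives 189 to 148 degrees/s, or −21.8%; with an assumed between-person SD of 12% that is 1.8 SD. The document does not support this reading. It gives neither the number nor the size of refixations and nowhere calls them small. If the 100 pixels are scene-camera pixels, 3 degrees lies below the counting threshold.

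Third, the ANOVA would not be wrong as a test: if the mix differs, the pooled means really differ. The error would lie in reading that as altered eye dynamics, and the protocol does not state that reading. This is right, and the point is limited accordingly.

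Fourth, nine shifts per task fits only the single-letter tasks. In tasks 3 and 4 participants search for a target letter, which adds search saccades in both groups. The figures therefore do not extend to those tasks.

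**Conclusion.** The point holds as a limited caution. As stated, the comparison of mean saccadic velocity confounds eye dynamics with saccade mix, and the study's own first hypothesis predicts that the mix will differ. The likeliest result is apparent slowing in cases: about 5% to 14% in the single-letter tasks for 5 to 7 degree refixations and at least a doubling of their number. For a modest excess it is about 2% to 4% (10 v 13). The direction can reverse if refixations are larger than the letter shifts.

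These sizes rest on an assumed amplitude-velocity relation that was not varied, and on assumed counts, refixation sizes and between-person spread. None of these is given in the document. Because velocity is exploratory and lies outside the hypotheses and listed outcomes, the main conclusions of the study are not touched.

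**What to change.** If saccadic velocity is reported, replace the comparison of raw means by one of these:

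- **Matched amplitude**: a mixed model of log velocity on log amplitude and group, with participant random effects, reporting the group difference at a stated amplitude.
- **Separate classes**: analyse letter-to-letter saccades apart from refixations, taking target distance into account.

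In either case, state that the unadjusted mean will not be given an ROC threshold and will not be interpreted as altered eye dynamics.

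The cost is slightly more analysis, and velocity and amplitude must be exported for each saccade from the eye-tracker software. The article mentions only counts and durations as output, so the availability of that export should be confirmed. No new data collection is needed if it is available. The Results section says that collection is complete and analysis has yet to begin, so the change can be made beforehand.

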## Methods

### Aim

To conduct an observational study with 40 adults (20 in each group; healthy adults and adults with motion sensitivity). The study will determine whether complex visual environments are associated with fixational instability, altered COP displacement, and altered center of mass (COM) displacements of the head and body in adults with motion sensitivity compared with healthy adults.

### Hypothesis

Complex visual environments in people with motion sensitivity compared with healthy adults will be associated with (1) increased number of visual refixations, (2) increased displacement of COP, and (3) differences in the body COM displacement and differences in the head COM displacement.

### Trial Design, Setting, and Participants

This is a cross-sectional exploratory single-session experimental study that will be laboratory based in Auckland University of Technology. A total of 40 adults will participate in the study (20 healthy adults and 20 adults with motion sensitivity after vestibular disorder). Healthy adults aged between 18 and 60 who are independently mobile and have no history of neurological conditions will be recruited through neurorehabilitation research team networks and community advertisements. Adults with motion sensitivity will be recruited through a specialized vestibular disorders clinic. They will be included if they have had a history of vestibular disorder (confirmed by a clinician in the vestibular disorder clinic) but have no current signs of acute vestibular deficits, are aged between 18 and 60 [40,41], have a history of motion sensitivity symptoms as reported by the Visual Vertigo Analogue Scale (score >5) [42-44], and score >40 on the Dizziness Handicap Inventory [44]. People with a history of previous eye surgery, or a medical condition that may influence eye movements such as sarcoidosis, Lyme disease, diabetes mellitus, traumatic brain injury, and migraine will be excluded from the study.

### Recruitment

Potential participants will be provided with a Participant Information Sheet and be requested to contact the corresponding author by email or telephone. All potential participants will be made aware that participating in this study will not influence their current health care.

### Screening

Potential participants will be screened against the study’s inclusion and exclusion criteria via telephone or through a face-to-face meeting with the researcher (SC). Eligible potential participants will be asked to provide written informed consent.

### Experimental Setup

The experimental setup consists of a projector screen (Brateck Lumi), a mobile eye tracker device (SensoMotoric Instruments), a force plate (Advanced Mechanical Technology Inc.), and a 3D motion capture system (Qualisys Motion Analysis Capture System; Qualisys Medical AB). Visual fixations will be recorded using a mobile eye tracker (SMI BeGaze; SensoMotoric Instruments). A 3D motion capture system and a force plate will be used to record kinematics and postural sway, respectively. The projector screen (135 in., 16:9 aspect ratio) will be mounted at 3.5-m distance from the force plate for projecting the visual environments (Figure 2).

**Figure 2 figure2:**
[figure not shown]
The experimental setup.

#### Sensor Motoric Instruments Eye Tracking Glasses (SMI ETG)

The SMI Eye Tracking Glasses (SMI ETG) are a mobile eye-tracking device with a binocular sampling rate of 120 Hz (Figure 3). SMI uses infrared light of wavelength around 789-880 nm to increase the contrast between the pupil and iris which is easily detected by the camera. SMI is a video-based eye tracker based on the concept of pupil center corneal reflection. The scene camera has a resolution of 1280 × 960 pixels @ 24FPS, 960 × 720 pixels @ 30 FPS with a 60° horizontal and 46° vertical field of view. The gaze position accuracy is 0.5° for all distances and the gaze tracking range is 80° horizontal and 60° vertical.

The SMI software uses a frame-by-frame analysis of the gaze data. These data involve defining the location and type of gaze behavior for each frame of data collected. Frame numbers are used to determine the duration of the eye movement. SMI uses an in-built detector for identifying saccades, fixations, and blinks. According to the detector, a blink is identified by points where eye data are not present, a saccade represents a quick change in gaze location, and a fixation is bordered by 2 saccades.

Data collected by the eye-tracking glasses identify the primary event as fixation and therefore a dispersion-based algorithm is used. The algorithm identifies fixations as groups of successive points within a dispersion, or maximum separation. A blink is determined based on the whole trial data where the pupil diameter is either zero, or the horizontal and vertical gaze positions are zero, or they lie outside a calculated valid pupil range. Once fixations and blinks are identified, a saccadic event is created between the detected blinks and fixations.

